#### Effect evaluation secondary outcome parameters

Differences in secondary outcome parameters will be compared per subgroup using a similar mixed-effects model, adjusted for relevant covariates, to that used for the primary outcome. The relative contribution of preference for intervention or comparator on the primary outcome will be examined using stepwise logistic regression on all baseline parameters. Similar models will be built to examine the associations of PROMs, Scolioscope, Bunnell scoliometer, changes in radiographic parameters, clinical suspicion of curve progression or patient-reported postoperative complications, number of appointments at outpatient clinic, and number of radiographs with the primary outcome.

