### Study interventions

#### Patient-empowered follow-up (PE-FU) protocol (Figure 2)

The PE-FU protocol consists of patient-reported outcome measures (PROMs), the Scolioscope and clinical assessment including physical examination by the physician. The Scolioscope is a self-assessment tool that measures the trunk rotation, similar to what is measured with the Bunnell scoliometer (Figure 3). At baseline and at last follow-up (24 months) biplanar radiographs are taken. Instead of routine radiographs, at all intervening follow-up visits radiographs will only be taken when curve progression or postoperative complications are suspected based on so-called “sense of alarm” criteria, which is a signal for the treating physician to consider whether a radiograph is appropriate.

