### Patient characteristics and outcome measures (Table 2)

At baseline, relevant patient characteristics are collected to describe the study sample, including the 3 different subgroups. Primary outcome is defined as the proportion of radiographs that has led to treatment consequences in each subgroup (pre-treatment, post-brace, post-surgery). A treatment consequence is defined as start of brace therapy or any surgical intervention. Secondary outcome measures include both patient and clinician-reported outcomes.

**Table 2 T0002:** Baseline characteristics, secondary outcome measures, and measurement moments

Variable	Month of follow-up assessments					
	Baseline	3	6	12	18	24
Post-surgery group	√	√	–	√	–	√
Pre-treatment group and post-brace group	√	–	√	√	√	√

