### Limitations

First, the clinically relevant cut-off points for so-called “sense of alarm” of the existing PROMS for AIS follow-up are unknown. This is a secondary outcome of the study and has been accounted for by pre-defining “sense of alarm” criteria. Secondary analyses are planned to determine the relevant sense of alarm criteria. Second is the logistic complexity of the study. Due to this complexity a risk of delay in recruitment might exist. Regular meetings (face-to-face and online) with the local study teams will be planned, to start the study, to discuss possible solutions on the different (logistic) challenges that emerge, and thus to support patient recruitment.

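### The planned association models list the radiograph's own finding beside the signals that precede it; entered jointly, it would attenuate those signals and make the models unsuitable for setting the sense-of-alarm criteria

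*Protocol article*

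**What the plan says.** All references are to the protocol article.

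- **Outcome.** Patient characteristics and outcome measures: "Primary outcome is defined as the proportion of radiographs that has led to treatment consequences in each subgroup". The same section adds: "A treatment consequence is defined as start of brace therapy or any surgical intervention".
- **Predictors.** Effect evaluation secondary outcome parameters: "Similar models will be built to examine the associations of PROMs, Scolioscope, Bunnell scoliometer, changes in radiographic parameters, clinical suspicion of curve progression". The list goes on to patient-reported postoperative complications and ends with "number of appointments at outpatient clinic, and number of radiographs with the primary outcome".
- **Model family.** The sentence just before says that the contribution of preference will be "examined using stepwise logistic regression on all baseline parameters". This is the nearest model to which the word similar can refer.
- **When the alarm is used.** In the PE-FU protocol section, at the visits between baseline and 24 months, "radiographs will only be taken when curve progression or postoperative complications are suspected". The alarm is described there as something "which is a signal for the treating physician to consider whether a radiograph is appropriate".
- **Where the criteria come from.** Limitations: "Secondary analyses are planned to determine the relevant sense of alarm criteria". It does not say which analyses these are.
- **Another route.** The abstract names positive predictive value, and the interrelation of clinical assessment, quality of life and parameters for starting treatment, as secondary outcomes.

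**The concern.** The predictor list mixes two kinds of variable. PROMs, Scolioscope, scoliometer and clinical suspicion can be known before a radiograph is taken. Change in radiographic parameters is what the radiograph shows. It cannot help decide whether to take that radiograph, and it lies on the path from a signal of progression to the decision to treat.

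A useful alarm signal is one that predicts what the radiograph would show. A model that holds the radiographic finding fixed removes that part of the signal's value and keeps only what the signal adds once the image has been seen. Stepwise selection would make this worse: a strong post-radiograph variable tends to enter early, and the correlated signals are then judged conditional on it.

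What is at stake is the reading of a secondary analysis. The scoliometer, Scolioscope or PROMs could look weaker than they are as triggers for a radiograph, in a study whose Discussion says that it will contribute to evidence-based guidelines.

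**Working it through.** The article gives no figure for these models, so there is none to reproduce. The check is one of model structure, with a simulation to show size.

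**Structure.** Let C be the Cobb change seen on the radiograph and S a pre-radiograph signal, both in SD units with correlation r. Let Y be the treatment consequence, with

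logit P(Y) = a + βC + δS.

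- With C in the model, the coefficient of S estimates δ, the direct effect only.
- Without C, the slope of the linear predictor on S is δ + βr. The logistic estimate comes out somewhat smaller, because the part of C that S does not explain shrinks it.
- Adding C therefore removes the βr part. If δ = 0, nothing is left, whatever r is.

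**Inputs.**

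- From the Appendix, pre-treatment group: 60 patients per arm and 4 follow-up assessments, so 60 × 4 = 240 radiographs in one S-FU arm. The incidence per radiograph is 23%/4 = 5.75%, taken as about 6%. This gives about 14 consequences (240 × 0.06 = 14.4).
- A second size of 480 radiographs (2 × 240) was also run.
- Assumed, not in the documents: r = 0.3, 0.5 or 0.7; β = 2.0; δ = 0, 0.5 or 1.0 log-odds per SD. There were 300 runs per setting. Repeated radiographs of one patient were treated as independent.

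**Expected slope before shrinkage, δ + 2r**, at r = 0.3 / 0.5 / 0.7: 0.6 / 1.0 / 1.4 for δ = 0; 1.1 / 1.5 / 1.9 for δ = 0.5; 1.6 / 2.0 / 2.4 for δ = 1.0.

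**Simulated results, 240 radiographs** (median log-odds ratio per SD of the signal; share of runs with P < 0.05):

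| δ | r | Without Cobb change | With Cobb change |
|---|---|---|---|
| 0 | 0.3 | 0.48; 38% | 0.00; 6% |
| 0 | 0.5 | 0.80; 81% | 0.04; 4% |
| 0 | 0.7 | 1.16; 98% | 0.00; 4% |
| 0.5 | 0.3 | 0.89; 82% | 0.56; 34% |
| 0.5 | 0.5 | 1.19; 98% | 0.47; 19% |
| 0.5 | 0.7 | 1.60; 100% | 0.55; 15% |
| 1.0 | 0.3 | 1.24; 98% | 1.07; 82% |
| 1.0 | 0.5 | 1.58; 99% | 1.05; 66% |
| 1.0 | 0.7 | 1.97; 100% | 1.01; 46% |

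**With 480 radiographs** the medians are much the same. The share with P < 0.05 once Cobb change is added is 6-7% for δ = 0, 27-54% for δ = 0.5 and 77-97% for δ = 1.0. Without Cobb change it is 66-100%, 99-100% and 100%.

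The medians without Cobb change lie somewhat below δ + 2r, and those with it lie close to δ, as the structure predicts.

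**The case against.** **Joint entry is not stated.** The article speaks of models, in the plural, and of associations. Separate one-variable models would satisfy the wording, and in them no signal's estimate is biased by the radiographic finding. This stands: the attenuation is conditional on joint entry. Similarity to a stepwise regression makes joint entry the natural reading, but no more than that.

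**The link to the alarm criteria is inferred.** Limitations does not name these models, and the list contains counts of appointments and radiographs, which look more like general correlates than visit-level triggers. This also stands. Even so, no other model described in the article relates PROMs, Scolioscope, scoliometer and suspicion to treatment consequence.

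**A reader might infer that the signals will appear worthless and that the criteria cannot be determined.** The documents do not support that. Complete loss needs Cobb change to carry the whole effect. Direct routes are plausible, above all after surgery, where any surgical intervention counts as a consequence and suspected complications can raise the alarm. With a direct effect, the signal survives in part. One-variable models and the positive predictive value also remain available.

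**A null adjusted coefficient is not false in itself.** It correctly answers whether a signal adds anything once the radiograph has been read. It misleads only if used to decide when to take one.

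**The illustration has limits.** It uses the S-FU yield. The article assumes 23.3% per radiograph for PE-FU in the pre-treatment group, which was not simulated. Table 2 collects the Scolioscope in PE-FU only, so the simulated figures do not speak to it.

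**Detail may be left to the analysis plan.** That would answer a missing specification. Here the article itself fixes the predictors, the outcome and, by reference, the model family, and an analysis plan that followed it would inherit the problem.

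**Conclusion.** The concern holds in conditional form. The article does not separate what is known before the radiograph from what the radiograph shows. If both enter one model, the signals' associations are attenuated: to about nil when treatment follows Cobb change alone, and only partly when a signal also acts directly. In the simulation with 240 radiographs, the share of runs with P < 0.05 fell from 38-98% to 4-6% in the first case, from 82-100% to 15-34% with a direct effect of 0.5, and from 98-100% to 46-82% with a direct effect of 1.0. These figures rest on assumed correlations and effects and on independent radiographs. They are not forecasts for the trial.

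Such joint models are unsuitable for determining the alarm criteria, because the alarm is used before the radiograph. The stronger reading, that the criteria cannot be determined at all, does not follow. The primary comparison, the sample size and the economic evaluation are not affected. The change is worth making because the bias is foreseeable and cheap to avoid.

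**What to change.** - State which models are meant to inform the sense-of-alarm criteria. In those models, use only information recorded at or before the visit at which the radiograph is considered.
- Leave changes in radiographic parameters out of their predictors. Leave out counts of appointments or radiographs that accrue after that visit; the article does not say how these are counted.
- Analyse change in Cobb angle as the dependent variable of a parallel model with the same predictors. A continuous outcome also carries more information than a rare yes/no event.
- Restrict models that include the Scolioscope to PE-FU patients, where it is collected. Note when reporting them that, between baseline and 24 months, Cobb change in this arm is seen only where a radiograph was taken.
- If the link between radiographic change and treatment is of interest, report it separately and not as evidence on when to take a radiograph.

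The cost is a few sentences in the analysis plan and a small amount of extra analysis. No new data are needed.

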#### Economic evaluation

An economic evaluation will be performed per subgroup for quality-adjusted life years (QALYs), treatment consequence (primary outcome), the number of radiographs (secondary outcome), and condition-specific quality of life questionnaire (SRS22r). Missing data will be imputed using multivariate imputation by chained equations and pooled estimates will be calculated using Rubin’s rules [16]. Cost and effect differences will be estimated using seemingly unrelated regression (SUR) analyses or mixed models, depending on the degree of clustering of data [17,18]. Incremental cost-effectiveness ratios (ICERs) will be calculated by dividing the differences in costs by those in effects. Bias-corrected and accelerated bootstrapping with 5,000 replications will be used to estimate the uncertainty surrounding ICERs and 95% confidence intervals around cost differences. Uncertainty will be shown by plotting cost-effectiveness planes and cost-effectiveness acceptability curves. Sensitivity analyses will be performed to assess the robustness of the results.

### Registration, ethics, data management, funding, and disclosures

Prior to the start of inclusion, the study was registered at clinicaltrials.gov (NCT05379127). Ethical approval was obtained by the Medical Ethics Committee (METC; NL77456.091.21). The study will be conducted according to the principles of the Declaration of Helsinki(19) and in accordance with the Medical Research Involving Human Subjects Act (WMO).

In all participating centers, the study protocol will be approved by the local research ethics board. Any substantial amendments will be notified to the accredited METC.

Data will be managed and archived for 15 years at the initiating center (Radboud University Medical Center). For data sharing and management, we intend to comply with the FAIR principles (Findability, Accessibility, Interoperability, and Reusable). All included patients receive a unique trial code, which pseudonymizes their personal data. All data will be coded, stored, and archived following the rules for good clinical practice (GCP). Handling of personal data will comply with the general data protection regulation (GDPR). The outcome data is only accessible for authorized research personnel of the research team at the initiating center, and monitoring and quality assurance personnel. The results from the study will be submitted for publication in peer-reviewed journals and presented at international conferences. This trial is supported by the Dutch Organization for Health Research and Development (ZonMw project number: 10330022010004). In addition to having received the research grant to perform the study, one author has a conflict of interest regarding the Scolioscope. Complete disclosure of interest forms according to ICMJE are available on the article page, doi: 10.2340/17453674.2024.40904

### Steering committee and quality assurance

A steering committee, including an orthopedic spine surgeon, an independent orthopedic surgeon, epidemiologist, patient representative, health technology assessment (HTA) expert, statistician, and implementation specialist, is supported by 8 orthopedic spine surgeons (region coordinators) to ensure acceptance of the study in the AIS consortium. An independent trial bureau (Trialbureau Zorgevaluatie Nederland) has been appointed to assure the quality of the study and to perform data monitoring. Monitoring will be performed in compliance with good clinical practice (GCP), in order to achieve high-quality research and secure patient safety.

## Discussion

This is the largest national and multicenter pragmatic randomized trial addressing the optimal frequency of radiographic follow-up in patients with AIS. It has the following strengths: it is the first study that includes patient-empowered follow-up for AIS, is an inclusive study with 3 follow-up-subgroups and few exclusion criteria, and has preference cohorts alongside the RCT to amplify generalizability. The study is designed as a nationwide multicenter partially randomized preference trial to compare PE-FU with S-FU to avoid unnecessary radiographs in the follow-up of patients with AIS. Patient follow-up is currently based on consensus-based guidelines [4,5]. To our knowledge, this study is the first to compare routine radiographic follow-up with a new patient empowered protocol for follow-up of patients with AIS. This will contribute to the development of evidence-based guidelines.

As an increased incidence of cancer has been reported later in life for patients with AIS receiving radiological follow-up during childhood, this study is relevant for all phases of AIS treatment described in this project [6,7], as the expected number of radiographs will be reduced in the new PE-FU protocol. Standard frequency of radiological follow-up is different in each of the subgroups (pre-treatment, post-brace, and post-surgery). For each subgroup, different indications for a radiograph could exist. This means that the different study objectives will be studied for each subgroup separately and the sample size analysis of each RCT in this study will be performed accordingly.

### Strengths

First, a strength of this study is the preference cohorts alongside the RCTs for each follow-up subgroup. By including preference cohorts, which follows clinical practice, generalizability of study results could be studied while the internal validity is assured and selection bias is reduced. The addition of the preference cohorts also supports implementation of trial results [20]. This design fits with the preferences of the patient panel involved in the grant application for this project [21]. An example of this design is the BrAIST -trial (brace study among patients with AIS) that started as an RCT and ended as an RCT combined with patient preference cohorts. During this trial the design was adapted and, by including a preference cohort, both the randomized groups and the preference cohorts could be completed [20].

Second, the expected risks from participation in the intended study are considered negligible. No risks are associated with the tools used in the study (PROMs, Bunnell scoliometer, Scoliscoop), because these tools are used within the intended indication. For the pre-treatment and post-brace subgroups, a potential but limited risk might exist. The detection of curve progression might be delayed and, consequently, the subsequent initiation of treatment. Due to safety and ethical considerations and to minimize this risk of late detection, the patients who participate in the new PE-FU will still come to the hospital for clinical examination. In addition, to achieve high-quality research and secure patient safety, Trialbureau Zorgevaluatie Nederland is involved in this study to give support in study logistics and to perform the monitoring.

### Limitations

First, the clinically relevant cut-off points for so-called “sense of alarm” of the existing PROMS for AIS follow-up are unknown. This is a secondary outcome of the study and has been accounted for by pre-defining “sense of alarm” criteria. Secondary analyses are planned to determine the relevant sense of alarm criteria. Second is the logistic complexity of the study. Due to this complexity a risk of delay in recruitment might exist. Regular meetings (face-to-face and online) with the local study teams will be planned, to start the study, to discuss possible solutions on the different (logistic) challenges that emerge, and thus to support patient recruitment.

## Appendix

### Detailed explanation of sample size calculation

The sample size is based on identifying superiority of the PE-FU in each individual RCT. The sample size is determined to have sufficient power to detect clinically relevant progression of the deformity leading to a treatment consequence. This partially randomized preference trial consists of 3 RCTs and 3 prospective preference cohorts for each treatment arm. The 3 subgroups for this study differ in nature, and as such we calculated the required separate sample sizes for each of the 3 RCTs. Our previous survey of patients with AIS showed that 50% of patients had a preference for 1 of the 2 cohorts (the preference cohorts) and 50% were willing to participate in the RCT. Thus, by doubling the sample size needed for the RCTs, the total sample size is achieved (RCTs and preference cohorts). As no previous studies regarding this subject are available, we searched the literature for patient samples with AIS that resemble our study population and that showed progression of the curve during natural history [14] or after surgery [15]. Assumptions were made based on the literature and expert opinion. Typically, patients with AIS and their caregivers/parents are very compliant with follow-up. Although complete adherence to the follow-up protocols of both the comparator (S-FU) and PE-FU is expected, a 10% dropout or lost-to-FU for the 3 subgroups is expected.

*Usual/S-FU care (comparator):* Although large practice variation exists, a recent survey showed that the average follow-up interval for routine radiographs was 6 months for the pre-treatment and post-brace group and 3 months for the post-surgery group. For all 3 groups biplanar full spine radiographs (PA and lateral) will be obtained at baseline, uniplanar full spine radiographs (PA) at follow-up for the pre-treatment and post-brace group, and biplanar full spine radiographs for the post-surgical group will be obtained. Consensus and acceptance was obtained among the scoliosis centers to define this as usual/S-FU care. In summary:

For the pre-treatment and post-brace group this means:

- Biplanar full spine radiographs (PA and lateral) at intake (baseline assessment study).
- Uniplanar full spine radiographs (PA) at 6, 12, 18 months’ follow-up.
- Biplanar full spine radiographs (PA and lateral) at 24 months’ follow-up at the end point of study (study purpose).
- In total, 2 biplanar and 3 uniplanar full spine radiographs (i.e., 5 assessments with 7 full spine radiographs).
- For the postoperative group this means:
- Biplanar full spine radiographs (PA and lateral) directly postoperatively (baseline assessment study), and at 3 and 12 months’ follow-up.
- Biplanar full spine radiographs (PA and lateral) at 24 months’ follow-up at the end point of study (usual care).

In total, 4 biplanar full spine radiographs (i.e., 4 assessments with 8 full spine radiographs)

### Explanation of the sample size calculation per subgroup

#### Pre-treatment group

In the literature, a 23% risk of curve progression was described [25] (i.e., comparator; usual/S-FU care). In the pre-treatment group, routine follow-up takes place every 6 months for a duration of 24 months (i.e., 4 follow-up assessments). Consequently, the incidence of progression per radiograph is 5.75% (i.e., 23%/4) for the control group/S-FU group. Based on the literature and expert opinion, a 5% margin is allowed for the PE-FU and 20% extra radiographs are expected for this group. The margin of 5% results in 28% risk of curve progression for the investigational group/PE-FU group (23% + 5% = 28%). Therefore, the incidence of progression per radiograph is expected to be 23.3% (i.e., 28%/1.20) for the PE-FU group (intervention/investigational group). For the increase in incidence/radiograph from 5.75% to 23.3%, the calculated sample size is 60 patients per arm (given a 95% CI and 80% power). Taking into account the expected loss to follow-up/dropout (10%), the final sample size is 66 patients for each treatment arm in the pre-treatment group.

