#### Effect evaluation primary outcome parameter

To evaluate the difference in clinical effectiveness of both follow-up protocols, the number of radiographs with treatment consequences will be divided by the total number of radiographs in each subgroup (pre-treatment, post-brace, post-surgery). To compare the primary outcome between the PE-FU group and the S-FU group, Pearson’s chi-square test is used. To evaluate the effect according to subgroups, linear mixed-effects models that account for repeated measurements will be performed, adjusted for scoliosis center and relevant baseline covariates. Assumptions of linear mixed modelling will be assessed and if needed variable transformations will be performed. Furthermore, for each subgroup the results of the RCT follow-up protocols will be compared with the similar preference cohort to indicate generalizability of study results.

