#### Post-brace group

In this group also, 23% of the patients have a risk of curve progression [14] (i.e., comparator; usual/S-FU care). The routine follow-up takes place every 6 months for a duration of 24 months (i.e., 4 follow-up assessments). Therefore, the incidence of progression per radiograph is 5.75% (i.e., 23%/4) for the control group/S-FU group. With a 5% margin for the PE-FU group, the risk of curve progression for the investigational group/PE-FU group will be 28%. We expected an increase of 15% based on expert opinion in the number of radiographs in the PE-FU post-brace group. Consequently, the expected incidence of progression per radiograph is 24.3% (i.e., 28%/1.15) in the PE-FU group. Based on the increase in incidence per radiograph from 5.75% to 24.3%, each arm of the post-brace group was calculated to consist of 55 patients (given a 95% CI and 80% power). With an expected loss to follow-up/dropout of 10%, each treatment arm of the post-brace group includes 61 patients.

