#### Post-surgery group

Based on a recent study among patients with AIS, no progression in the surgical area is expected [31]. Adding-on is a radiological complication that indicates progression of the curve under or above the instrumented curve. The expert opinion for clinically relevant prevalence of adding-on is 10% (i.e., comparator; usual care), with a 5% margin for PE-FU (i.e., 15%). The routine follow-up takes place at 3, 12, and 24 months after surgery (i.e., 3 follow-up assessments with biplanar full spine radiographs = 6 radiographs). The incidence of adding-on per radiograph is 1.7% (i.e., 10%/6) for the control group/S-FU group. The risk of adding-on for the investigational group/PE-FU group will be 15% (prevalence of 10% with a 5% margin for PE-FU). The expected extra number of radiographs in the post-surgery group is 5% (expert opinion). Therefore, the incidence of adding on per radiograph is expected to be 14.3% (i.e., 15%/1.05). For the increase in incidence/radiograph from 1.7% to 14.3%, the calculated sample size is 69 patients per arm (given a 95% CI and 80% power). Considering a 10% dropout and/or loss to follow-up, the final sample size is 76 patients per treatment arm for the post-surgery group.

Based on the above (literature and expert opinion), for this study a total of 812 patients is required (alpha 0.05; power 0.80). This means 66 per arm for the RCT pre-treatment, 61 per arm for the RCT post-brace, and for the RCT post-surgery 76 per arm (subtotal of patients in the RCTs is 406). The preference cohorts consist of the same arms as the three RCTs. For each arm (preference cohort) a similar number of patients is required (subtotal of patients in the preference cohorts is 406 patients).

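### The appendix adds an allowed 5-point margin to the PE-FU event risk in all three RCTs, so extra progression counts as benefit; with equal progression the post-surgery RCT has about 53% power, not 80%.

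*Protocol article*

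**What the plan says.** The appendix on sample size sets the aim: "The sample size is based on identifying superiority of the PE-FU in each individual RCT". Under Effect evaluation primary outcome parameter, "the number of radiographs with treatment consequences will be divided by the total number of radiographs in each subgroup", and the arms are compared as follows: "To compare the primary outcome between the PE-FU group and the S-FU group, Pearson’s chi-square test is used". A higher proportion therefore favours PE-FU.

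The appendix allows PE-FU a margin of 5 percentage points and adds it to the PE-FU risk in every subgroup:

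- Pre-treatment: "The margin of 5% results in 28% risk of curve progression for the investigational group/PE-FU group (23% + 5% = 28" per cent).
- Post-brace: "With a 5% margin for the PE-FU group, the risk of curve progression for the investigational group/PE-FU group will be 28" per cent.
- Post-surgery: "The risk of adding-on for the investigational group/PE-FU group will be 15% (prevalence of 10% with a 5% margin for PE-FU").

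Each raised risk is divided by the expected number of PE-FU radiographs (1.20, 1.15, 1.05). The results (23.3%, 24.3%, 14.3%) are set against S-FU rates of 5.75%, 5.75% and 1.7%. This gives 60, 55 and 69 patients per arm, or 66, 61 and 76 after dropout, and the closing statement that "for this study a total of 812 patients is required (alpha 0.05; power 0.80").

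The introduction gives the purpose as fewer radiographs without negative consequences for the patient's treatment, and the hypothesis as a safe reduction.

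**The concern.** An amount by which one arm is allowed to do worse normally enters a comparison as a limit, and it makes the claim harder or easier to reject at that limit. Here it enters as part of the expected effect. The superiority test looks for a higher proportion under PE-FU, so 5 more points of progression or adding-on in that arm widen the gap to be detected. The more progression PE-FU is assumed to have, the smaller the trial appears to need to be.

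If PE-FU does what the introduction hopes, progression is about the same in both arms and the gain comes only from taking fewer radiographs. The stated 80% was not computed for that case. A non-significant result could then be read as coming from an 80%-powered RCT when the power under that scenario was much lower.

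**Working it through.** **Inputs (appendix, per-subgroup explanation).**

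- S-FU rate p1: 23%/4 = 5.75% for pre-treatment and post-brace; 10%/6 = 1.67% for post-surgery.
- PE-FU radiographs per patient: 1.20, 1.15, 1.05.
- Patients per arm: 60, 55, 69 before dropout.
- 1:1 allocation, 80% power, alpha 0.05. Sidedness is not stated; I take the appendix's reference to a 95% CI to mean two-sided.

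**Step 1. Reproduce the plan.** Unpooled two-proportion formula: n = (1.96 + 0.8416)² × V / d², with V = p1(1−p1) + p2(1−p2), d = p2 − p1, and (1.96 + 0.8416)² = 7.849.

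- Pre-treatment, p2 = 28%/1.20 = 0.2333: 7.849 × 0.23308 / 0.17583² = 59.2, so 60.
- Post-brace, p2 = 28%/1.15 = 0.2435: 7.849 × 0.23839 / 0.18598² = 54.1, so 55.
- Post-surgery, p2 = 15%/1.05 = 0.1429: 7.849 × 0.13884 / 0.12619² = 68.4, so 69.

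All three match. Multiplying by 1.10 gives the stated 66, 61 and 76.

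**Step 2. Remove only the 5 points.** Equal progression gives p2 = 23%/1.20 = 0.1917, 23%/1.15 = 0.2000 and 10%/1.05 = 0.0952.

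- Pre-treatment: 7.849 × 0.20912 / 0.13417² = 91.2, so 92 (plan 60).
- Post-brace: 7.849 × 0.21419 / 0.14250² = 82.8, so 83 (plan 55).
- Post-surgery: 7.849 × 0.10256 / 0.07857² = 130.4, so 131 (plan 69).

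**Step 3. Power at the plan's numbers.** Power = Φ(d/√(V/n) − 1.96).

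- Pre-treatment: Φ(0.13417/0.05904 − 1.96) = Φ(0.313) = 62.3%.
- Post-brace: Φ(0.14250/0.06241 − 1.96) = Φ(0.323) = 62.7%.
- Post-surgery: Φ(0.07857/0.03855 − 1.96) = Φ(0.078) = 53.1%.

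If nobody dropped out (66, 61, 76), the values would be 66.4%, 67.2% and 57.1%. A pooled-variance formula gives 60.7%, 60.9% and 51.9%, but it does not reproduce the plan's sample sizes (it gives 62, 57 and 72).

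**Step 4. Direction.** By the Step 3 formula, 10 extra points of progression under PE-FU give power of 92%, 92% and 94%. Five points fewer give 39%, 40% and 18%.

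**Step 5. Radiograph counts.** Steps 1 to 3 treat a per-radiograph rate as if each patient supplied one radiograph. The planned chi-square test divides by radiographs. I count follow-up assessments at the evaluable sample size: 4, 4 and 3 per S-FU patient, and 1.20, 1.15 and 1.05 per PE-FU patient, all treated as independent. The counts are 240 v 72, 220 v 63.25 and 207 v 72.45. The post-surgery S-FU rate is then 10%/3 = 3.33%.

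Power = Φ((d − 1.96·s0)/s1), with s0 the pooled and s1 the unpooled standard error. With equal progression:

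- Pre-treatment: (0.13417 − 1.96 × 0.03816)/0.04876 = 1.22, so 89%.
- Post-brace: (0.14250 − 1.96 × 0.04069)/0.05269 = 1.19, so 88%.
- Post-surgery: (0.06190 − 1.96 × 0.02958)/0.03667 = 0.11, so 54%.

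With the 5 points put back, the same calculation gives about 97%, 97% and 85%. In post-surgery the margin therefore separates 85% from 54%.

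**Step 6. Unit check for post-surgery.** The appendix counts six single films per S-FU patient but 1.05 radiographs per PE-FU patient.

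- Single films in both arms (6 and 2 × 1.05 = 2.10; 414 v 144.9 films; 1.67% v 4.76%): (0.03095 − 1.96 × 0.01498)/0.01878 = 0.08, so 53%.
- The appendix's mixed count (414 v 72.45; 1.67% v 9.52%): (0.07857 − 1.96 × 0.02114)/0.03506 = 1.06, so 86%. This figure depends on counting a biplanar assessment as two in one arm and, as I read the 1.05, as one in the other.

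**The case against.** **The chi-square test uses radiographs, so the 62% and 63% are artefacts of sizing by patients.** This largely stands. A reader might infer from Step 3 that the whole trial is underpowered. The document does not support that: on the unit it plans to analyse, pre-treatment and post-brace exceed 80% without the margin, provided that radiographs are independent. Only post-surgery is short on both bases, and there the radiograph-based figure requires counting in the same unit in both arms.

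**The stated power holds only if PE-FU harms patients.** That is an inference too far. The appendix speaks of a margin, not a safety margin, and bases it on literature and expert opinion. The introduction does not state numerical equality of progression. What can be said is that the stated power depends on assumed extra progression, and that equal progression is the natural scenario for a safe reduction.

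**The inputs are the wrong event.** A reader might set the progression and adding-on risks against the primary event ("A treatment consequence is defined as start of brace therapy or any surgical intervention") and conclude that the rates are inflated. The appendix says the sample size concerns clinically relevant progression that leads to a treatment consequence, and it uses a clinically relevant prevalence of adding-on. Whether the 23% already means progression to treatment depends on a cited source that is not at hand, so this is not established.

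**The 5 points are never used as a margin.** None of the analyses in the article does so, but a statistical analysis plan may exist that is not shown. Delayed initiation of treatment is a named secondary outcome, so the question of harm is measured. Neither fact changes how the 5 points enter the sample size.

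**The sums are right.** They are: the plan's figures reproduce exactly. The fault lies in where the margin is placed.

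**Conclusion.** The point holds as stated in the heading. In all three RCTs the allowed margin is placed in the numerator of the effect that favours PE-FU. It lowers the computed sample size from 92 to 60, 83 to 55 and 131 to 69 per arm, and it conflicts with the hypothesis of a safe reduction.

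With equal progression, power by the plan's own formula is about 62%, 63% and 53%. On radiograph counts it is about 89%, 88% and 54%. The shortfall is firm for post-surgery. For pre-treatment and post-brace it depends on the unit of analysis.

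These figures rest on a two-sided alpha of 0.05, the plan's own progression risks and PE-FU radiograph numbers, evaluable patients of 60, 55 and 69 per arm, and, for the second set, independent radiographs counted alike in both arms.

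**What to change.** - Remove the 5 points from the PE-FU numerator in all three subgroup calculations and recompute with equal event rates: 23%/1.20 = 19.2%, 23%/1.15 = 20.0% and 10%/1.05 = 9.5% on the plan's present scale.
- Restate the power of each RCT at the planned 66, 61 and 76 per arm (60, 55 and 69 evaluable). Name the unit of analysis and count radiographs in the same way in both arms.
- Do not count the 5 points as benefit. If they are kept, use them only as a limit on the between-arm difference in a patient-level outcome.

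The cost is a recalculation and a less favourable power statement, most clearly for post-surgery. No new patients are needed to make the correction.
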